### Study population

#### The first stage

In this section, the participants and population under investigation are adolescents (male and female students of Amol City schools), parents (father or mother or both), health professionals (specialists who have experience working in the field of adolescents and programming in the field of health) who are willing to participate and present their experiences and opinions in the field of designing and developing Self-care mobile application.

#### The second stage

The population studied at this stage are adolescents (boys and girls students of Amol schools), parents (father or mother or both), health professionals (specialists who have experience working in the field of adolescents), and the desire to participate and provide experiences and they have their own opinions in the field of questionnaire design.

#### The third stage

The studied population will be all adolescents aged 10–19 years old in Amol City and interested in knowingly participating in the research.

### Sampling method

#### The first stage

The sampling of adolescents is conducted purposefully with maximum diversity (considering factors such as age, sex, educational background, and parents’ education). Also, eligible parents or caregivers of adolescents will be invited and health professionals will be purposefully selected. Then, the interview is carried out until no new code is created through repeated and open questions and the data is saturated. Satisfaction with the study will be obtained before the interview and people will answer general and specific questions about mobile apps during the interview. In the stage of application usability evaluation, 15 male and female users and 15 specialists will be employed.

#### The second stage

To perform construct validity, based on the list prepared by the Department of Education, out of the 337 public schools and 93 non-governmental schools listed, six girls’ schools and six boys’ schools were randomly selected, and from each school and every grade, students of 10–19 years old were selected. The number of samples will be 5–10 times the questionnaire items.

#### The third stage

The next stage of the sampling method is cluster random. From 337 government schools and 93 non-government schools, based on the list of urban schools received from the Department of Education, two boys’ schools and two girls’ schools are randomly selected. Then, one boy’s school and one girl’s school will be randomly assigned as the intervention group and one boy’s school and one girl’s school will be in the control group, and the sampling of students of different grades of the selected schools will be simple cluster or random. Sampling of students from different grades from selected schools will be simple in cluster or random. The sample size was calculated according to the formula of 43 people in each group. Taking into account 15% attrition, the sample size was determined to be 50 people in each group. The study will be conducted on 100 students of Amol City. Of these, 50 people will be assigned to the intervention group and 50 people will be assigned to the control group. From each school, 25 samples were selected (Fig. 2).

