**Fig. 2 Fig2:**
[figure not shown]
The study sampling stages

$$n= \frac{{2\left(Z1-\frac{\alpha }{2}+ Z1-\beta \right)}^{2}}{{\left(\frac{\Delta }{S}\right)}^{2}}$$

The schools selected for the intervention and control groups will be far apart in order to prevent contamination bias. The effects of confounding variables such as economic status and social class will be controlled in the clusters in the data analysis with the covariance test. All samples, education office, school managers, and user panel managers will be blinded.

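### Stage 3 draws four schools from a mixed government and non-government list with sex as the only stated restriction, so the arms differ in sector in about half of draws, and covariance analysis cannot reliably correct this

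*Protocol article*

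**What the plan says.** The stage 3 part of the Sampling method section selects schools "From 337 government schools and 93 non-government schools, based on the list of urban schools received from the Department of Education". Two boys' and two girls' schools are drawn at random, and one school of each sex is randomised to each arm. On size it says "From each school, 25 samples were selected". Pupils are taken from different grades by a method given as either cluster or random sampling. The target age range is 10 to 19.

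The paragraph after Fig. 2 adds one further rule on schools: "The schools selected for the intervention and control groups will be far apart in order to prevent contamination bias". It then states how social differences will be handled: "The effects of confounding variables such as economic status and social class will be controlled in the clusters in the data analysis", using a covariance analysis.

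Stage III of the Study process section describes a pre-test and post-test design with a control group. The self-care questionnaire is completed before the app period and again after three months.

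Sex of school is the only stratifier in the text. No restriction or matching on sector, grade range or neighbourhood is stated.

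**The concern.** The article itself names economic status and social class as confounders. Sector of school is an obvious school-level marker of both, and the list is reported by sector. With two schools per arm, a free draw gives little protection against an unequal sector mix in the one trial that will be run. Grade range is a second route: nothing requires the two schools of a sex to serve the same grades or to contribute equal numbers per grade.

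The remedy offered is covariance analysis. Schools are the randomised units and there are four of them, so the remedy has almost nothing to work with at that level. If pupils in one sector or grade band change differently over three months, part of that difference can be read as an effect of the app.

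**Working it through.** **Inputs.** From the Sampling method section: 337 government and 93 non-government schools; two boys' and two girls' schools; one of each sex per arm; 25 pupils per school. Assumption: the non-government share is the same among boys' and girls' schools, since the article does not give it by sex.

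**The plan's own figures.** Two schools × 25 pupils = 50 per arm, which agrees with the stated size. The step from 43 to 50 for 15% attrition also reproduces closely: 43 × 1.15 = 49.45, or 43/0.85 = 50.6. These figures do not bear on the point.

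**Chance of sector imbalance.**
- Share: q = 93/(337 + 93) = 93/430 = 0.2163.
- One same-sex pair is discordant on sector: d = 2q(1 − q) = 2 × 0.2163 × 0.7837 = 0.339.
- At least one of the two pairs is discordant: 1 − (1 − d)² = 1 − 0.661² = 0.563.
- Exactly one pair is discordant: 2d(1 − d) = 2 × 0.339 × 0.661 = 0.448.
- Both pairs are discordant in the same direction, so one arm is all government and the other all non-government: d²/2 = 0.057.
- The arms have unequal numbers of non-government schools: 0.448 + 0.057 = 0.506 (from unrounded terms).

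**Sensitivity.** Drawing without replacement, with 215 schools assumed for each sex and the 93 non-government schools split from 10/83 to 80/13 between the sexes:
- unequal numbers: 50.2% to 50.7%;
- at least one discordant pair: 52% to 57%;
- complete coincidence of sector with arm: 2% to 6%.

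The equal-share assumption therefore matters little for the main figure.

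**What covariance analysis can do at school level.**
- 4 schools − 2 arms = 2 degrees of freedom (two-sided 5% critical t = 4.30).
- With sex of school also fitted: 1 degree of freedom (critical t = 12.71).
- With sector, or any one school-level social covariate, also fitted: 0, so there is no error estimate.

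When exactly one pair is discordant (about 45% of draws), arm, sex and sector can all be fitted, but the model is saturated. The arm effect then rests on the difference between the two schools of the concordant pair. When both pairs are discordant in the same direction (about 6%), sector and arm are the same variable and cannot be separated.

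**What it can do at pupil level.** With 100 pupils, economic status measured on the pupil and the pre-test score can be fitted. The first removes only what is measured on the pupil. The second removes much of a stable difference between schools in self-care level. Neither removes a sector or grade difference in change over three months.

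**Effect of pairing.** If the two schools of each sex come from the same sector, d = 0 and the chance of sector imbalance between arms falls from about 51% to 0. The school-level degrees of freedom do not change.

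**The case against.** Several points on the other side are sound and limit the conclusion.

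- A reader might infer that a school difference, once present, cannot be removed afterwards. The documents do not support that. There is a pre-test, and adjusting for it can take out much of a stable difference in level. What survives is a difference in change.
- A reader might also infer that no school-level confounder can be separated from arm. That is too strong as well. Sector is fully aliased with arm in only about 6% of draws. In the other 45 or so percentage points of imbalance the arm effect is estimable with sector fitted; what is lost is any estimate of error.
- The 51% is a probability that sector labels are unequal, not a size of bias. The documents give no figure for the effect of sector on the self-care score or its change.
- Randomisation of schools is kept, so the imbalance is chance variation and not systematic bias. That is true over repeated draws, but two schools per arm give little protection in a single trial.
- That the distance rule widens the social gap is possible, but its effect cannot be calculated from the documents.
- Fig. 2 is not shown and might include a sector step, and the full protocol might add matching. The text as published states neither.
- The phrase about clusters could be read as pupil-level adjustment. That analysis is feasible, but it would not control social differences between the schools, which is where the arms are formed.
- Pairing adds no schools, so other school-level differences remain hard to adjust for.

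**Conclusion.** The point holds in a limited form. As written, the draw leaves the arms with unequal numbers of non-government schools about half the time (51%, range 50.2% to 50.7% over the splits tried), and makes sector identical with arm in about 6% (range 2% to 6%). This rests on random selection within sex from the stated list, with no sector step in the missing figure, and it ignores any effect of the distance rule. The statement that covariance analysis will control social class in the clusters cannot be delivered at the level randomised, because one school-level covariate exhausts the degrees of freedom. Stable differences in level can largely be handled through the pre-test; differences between sectors or grades in three-month change cannot. The size of any resulting bias cannot be computed from the documents. The change is worth making because it costs almost nothing.

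**What to change.** Within each sex, draw the two schools from the same sector and the same grade range, then randomise one of the pair to the app. Sample the same number of pupils per grade in both schools of a pair. The sector of each school is known from the list already held, and no extra pupils are needed. The cost is a somewhat more restricted selection of schools. Matching on neighbourhood economic status is optional, because the documents do not show that the list holds it.

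The schools may already have been drawn: the Trial status section gives a first recruitment day of July 26, 2022, before the protocol version of May 12, 2023. If so, report the sector and grade range of each of the four schools by arm.

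In either case, restate the paragraph after Fig. 2 to say that covariance analysis adjusts for economic status measured on the pupil and for the pre-test score, and that it cannot reliably remove school-level differences between the arms. This is a change of wording only.

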#### Stage III

The third stage is an interventional method of experimental study. This research will be conducted through a pre-test-post-test design with a control group. All the students studying in schools constitute the research community. The researcher first introduces the adolescents to the full explanation of the research and its goals. Then informed written consent will be obtained from the volunteers. None of the participants will be subject to any other research intervention. Schools will be randomly assigned to one of the two intervention (group 1) and control (group 2) groups. The full content of the program will be visible only to the participants in the intervention group. Participants in the control group will be able to download the app after the end of the intervention to use the educational benefits of the app. A self-care application can be used online and offline designed for smartphones running the Android operating system. To run this test, eligible students are asked to install the self-care app on their smartphone and see the necessary instructions on how to work with the program in the form of a short guide on the main page of the application. Initially, the participants are asked to complete the self-care questionnaire in the form of a pre-test. Then, the educational content designed for the application is provided for individuals based on national and international guidelines and protocols of (WHO, CDC, FDA, ADF, Ministry of Health and Medicine, Health Education and Health Promotion Office). This program will be available to people for 3 months and after installing the application on their smartphone and entering the information requested from the users, educational content and reminder messages will be sent according to their conditions. In the reminders section, the user registers his health behavior based on the day, time, and number of times he wants, and a reminder is sent to him. But if the user’s self-care status after answering the self-care questions in each of the 5 dimensions of self-care is assessed as weak or average, motivational health messages are sent to the user daily in the form of notifications, so that the user is encouraged to perform self-care behaviors. The use of the application by the participants is reviewed in the management panel and health messages and incentives are provided for the use of this program. To provide support, the researcher’s phone number is given to the subjects to make a call in case of problems. Three months after the intervention, when no new content is sent to the student, the participants in both groups are requested to complete the self-care questionnaire in the form of a post-test. After the end of the data collection process, the individuals in the control group can install a mobile Application and the necessary training will be given to them after the end of the study. In the present study, content, information, and experiences reach the end users or audience with the specific purpose of self-care through mobile applications in the form of text, audio, or other art forms. Users find and use health-related self-care information through content. The graphic design of the application is based on the opinion of the research team professional designers and application development experts. The production of the content is based on the points extracted from the interviews, national and international guidelines, and protocols of (WHO, CDC, FDA, Ministry of Health and Medicine, Health Education and Health Promotion Office), for example, Australian dietary guidelines, Canberra: NHMRC [20], WHO guidelines on physical activity and sedentary behavior for children and adolescents aged 5–17 years: summary of the evidence [21], and physical activity guidelines [22].

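### The stage 3 sample size of 43 (50 after attrition) per arm uses a formula for independent individuals, although four schools are randomised, two per arm, and no design effect is applied

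*Protocol article*

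**What the plan says.** The stage 3 part of Sampling method describes a cluster design: "The next stage of the sampling method is cluster random". Two boys' and two girls' schools are drawn from a list of 337 government and 93 non-government schools, and "one boy’s school and one girl’s school will be randomly assigned as the intervention group", with the other two as control. Study process, Stage III confirms the unit of allocation: "Schools will be randomly assigned to one of the two intervention (group 1) and control (group 2) groups".

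The same part of Sampling method gives the size: "The sample size was calculated according to the formula of 43 people in each group", then "Taking into account 15% attrition, the sample size was determined to be 50 people in each group", and "From each school, 25 samples were selected".

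The formula, printed with Fig. 2, is n = 2(Z(1−α/2) + Z(1−β))² / (Δ/S)². It contains no ICC, cluster size or design effect, and its symbols have no values. The text below it plans a covariance adjustment for economic status and social class in the clusters. Methods of analysis names the independent t-test, the paired t-test and analysis of variance.

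**The concern.** The formula assumes that each pupil contributes independent information. Pupils in one school share teachers, neighbourhood and peers, so their self-care scores are likely to be correlated. Because whole schools are allocated, that correlation goes directly into the variance of the arm difference. A size from this formula is then too small for any positive ICC.

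Two schools per arm also leave very few degrees of freedom for a comparison that respects the allocation. A null result from stage 3 would say little. If instead the independent t-test were run on pupils as though school did not matter, its false-positive rate would exceed the nominal level. This need not wait for an unseen analysis plan: the article itself prints the formula, its result and the unit of allocation, and they do not fit together.

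**Working it through.** **Inputs from the protocol article.** 43 per arm before attrition; 15% attrition; 50 per arm; two schools per arm; 25 pupils per school; the printed formula.

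**Assumptions, because no values are given.** Two-sided alpha 0.05 (the formula's Z(1−α/2) implies two-sided); power 80% or 90%; ICC 0.01, 0.02, 0.05 or 0.10.

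**Step 1: the plan's own 43.** It cannot be reproduced directly, so the formula is solved for d = Δ/S.
- 80% power: 2(1.960 + 0.842)² = 15.70; d = √(15.70/43) = 0.604.
- 90% power: 2(1.960 + 1.282)² = 21.01; d = √(21.01/43) = 0.699.

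The unclustered formula thus reaches 43 at ordinary inputs. The rise from 43 to 50 is attributed wholly to attrition, so no design effect sits in either number.

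**Step 2: attrition.** 43/(1 − 0.15) = 50.6, so 51. The stated 50 matches 43 × 1.15 = 49.45, and 50 × 0.85 = 42.5 completers. An assumed 80% power becomes 79.5%.

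**Step 3: clustering in the planned design.** With 43 completers per arm in two schools, m = 21.5. Design effect DE = 1 + (m − 1) × ICC; effective n per arm = 43/DE. The school-level test is a t-test on four school means, with 2 degrees of freedom, critical value 4.303 and noncentrality d/√(2·DE/43). For example, at ICC 0.05: DE = 1 + 20.5 × 0.05 = 2.025; 43/2.025 = 21.2; noncentrality at d = 0.604 is 1.97; power is 21%.

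| ICC (assumed) | 0.01 | 0.02 | 0.05 | 0.10 |
|---|---|---|---|---|
| DE | 1.21 | 1.41 | 2.03 | 3.05 |
| Effective n per arm | 36 | 30 | 21 | 14 |
| Power, 2 df, d ≈ 0.60 | 31% | 28% | 21% | 16% |
| Power, 2 df, d ≈ 0.70 | 38% | 34% | 26% | 20% |
| Approximate type I error of a pupil-level t-test ignoring school, 2(1 − Φ(1.96/√DE)) | 7% | 10% | 17% | 26% |

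**Step 4: can more pupils per school cure it?** With two schools per arm, effective n per arm cannot exceed 2/ICC: 200, 100, 40 and 20 over the same ICC range. At 0.05 and 0.10 that ceiling is below 43 however many pupils are added. At 0.01 it is not, but the 2 degrees of freedom remain.

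**Step 5: the same pupils in 12 schools.** Six schools per arm, m = 43/6 = 7.17, 10 degrees of freedom, critical value 2.228, same formulas.

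| ICC (assumed) | 0.01 | 0.02 | 0.05 | 0.10 |
|---|---|---|---|---|
| Power, d ≈ 0.70 | 81% | 79% | 72% | 63% |
| Power, d ≈ 0.60 | 69% | 66% | 60% | 51% |

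**The case against.** **The planned adjustment may already deal with clustering.** The covariance adjustment for economic status and social class could remove some between-school variation. It acts on named covariates only. It adds no school-level degrees of freedom and changes nothing in the formula that produced 43.

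**The power figures ignore the pre-test.** Stage 3 has a pre-test and a post-test, and adjusting for baseline could reduce both residual and between-school variance. This is fair. The percentages are illustrations for post-test school means, not firm bounds. The 2 degrees of freedom remain a severe limit.

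**No precision is claimed.** A reader might infer that the trial promises 90% power and misses it. The article does not support that: it gives symbols without values. The loss can be shown only against an assumed nominal power and an assumed ICC.

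**Attrition.** A reader might count the 50 as a second serious error. It is one pupil per arm and about half a point of power, so it is a text correction.

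**School type.** Schools are drawn without stated matching on government or non-government type, so a reader might infer that type is likely to coincide with arm. If boys' and girls' schools share the listed mix (an assumption), a same-sex pair is mixed with probability 2 × (337/430) × (93/429) = 0.34. Both pairs are then mixed in the same direction with probability 0.34²/2, or about 6%. At least one mixed pair is likelier, 1 − (1 − 0.34)² = 56%, but that is not full coincidence, and sex is balanced across arms by design.

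**Redesign may be too late or difficult.** Trial status dates first recruitment to July 2022, before the protocol version of May 2023, and the article wants intervention and control schools far apart. Both points stand, so a redesign can only be conditional.

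**Conclusion.** The point holds. The stated size does not fit the stated design: schools are randomised, the formula is for independent individuals, and no design effect enters 43 or 50. Any positive ICC brings the effective size below 43 per arm. Over ICC 0.01 to 0.10 it falls to between 36 and 14, and a school-level test has power of 31% down to 16% (d about 0.60) or 38% down to 20% (d about 0.70). These figures rest on an assumed two-sided 5%, the assumed ICC range, 21.5 completers per school and no baseline adjustment. The mismatch itself rests on none of them.

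The conclusion does not extend to a broken promise of power, a material attrition error or a likely confounding of school type with arm.

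**What to change.** **Text, whatever the recruitment status.** Restate the stage 3 sample-size paragraph. Give alpha, power, Δ and S; apply 1 + (m − 1) × ICC over a stated ICC range; and report the power or detectable difference that two schools per arm provide, allowing for the 2 degrees of freedom. Correct the attrition step to 51 per arm. This costs only text, and a less favourable figure in print.

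**Design, only if school selection is still open.** Spread the same 100 or so pupils over more of the 430 listed schools, for example 12 with about eight enrolled in each; stage 2 already samples from 12. Pair same-sex schools on government or non-government type before randomising within pairs. The gain is large, but the 12-school figures in Step 5 stay below 80% throughout at d of about 0.60 and below 90% throughout at d of about 0.70. The revised text should therefore not present the change as restoring nominal power. The cost is more school permissions and a harder task in keeping the two arms' schools far apart.

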#### Stage II

In the second stage, with an organized review of available sources and articles based on the concept of self-care, the items of the “Questionnaire for Measuring Self-Care Performance in Adolescents” will be extracted. Next, the validity (face, content, and construct) and reliability of the designed questionnaire will be determined.

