#### The second stage

At this stage, to determine construct validity, based on the list prepared by the Department of Education, six girls’ schools and six boys’ schools were randomly selected. From each school and each grade—within the 10–19-year-old age group—a class will be selected in a cluster random sample. The number of samples per item will be 5–10 samples. At this stage, we collect data using a questionnaire prepared in the previous stage, which has both face and content validity.

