#### The third stage

At this stage, we use a researcher-made questionnaire the validity and reliability of which were determined in the second stage. The desired questionnaire is uploaded on the application and after installation, this program will be available to people for 3 months. After 3 months of the intervention, by an SMS or a phone call, the people of both groups are asked to complete the questionnaire uploaded, which is in the form of a post-test, and send it back to the researcher. After collecting the data, analysis is conducted by statistical tests.

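### Stage 3 is sized with no between-school term for a score built only in stage 2, and the 12 stage 2 schools that could supply its SD and school variance are given no such use

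*Protocol article*

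**What the plan says.** **Size.** Under Sampling method, The third stage, the article says: "The sample size was calculated according to the formula of 43 people in each group". It continues: "Taking into account 15% attrition, the sample size was determined to be 50 people in each group". The formula printed with Fig. 2 is the usual one for two independent means, n = 2(Z₁₋α/₂ + Z₁₋β)²/(Delta/S)². It has no term for schools. No value or source is given for Delta, S, alpha or power.

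**Allocation.** Schools are the randomised unit: "one boy’s school and one girl’s school will be randomly assigned as the intervention group", with the other two schools as control. "From each school, 25 samples were selected".

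**Outcome.** For stage 3, "we use a researcher-made questionnaire the validity and reliability of which were determined in the second stage". Under Study process, Stage II, "the items of the “Questionnaire for Measuring Self-Care Performance in Adolescents” will be extracted", after which validity and "reliability of the designed questionnaire will be determined". The number of items is still open, because the stage 2 sample is given as 5 to 10 times that number.

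**Stage 2 data.** Six girls' and six boys' schools are drawn at random from the same list of 337 public and 93 non-governmental schools. In each school and grade "a class will be selected in a cluster random sample". Methods of analysis names factor analysis for this stage.

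**Stage 3 analysis.** Methods of analysis gives independent and paired t-tests and analysis of variance. The sampling section adds covariance adjustment for economic status and social class.

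**The concern.** A stage 3 size for this outcome in this design needs two quantities: the SD of the score and the variance between schools. The figure of 43 uses the first only through an unexplained ratio and leaves out the second. Stage 3 cannot usefully supply the second, since four schools in two arms leave almost no between-school information. Stage 2 measures the same score in 12 schools of the same city, so it could supply both, yet the article gives it no such role.

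If the plan is followed as written, the stated size promises more than four schools can deliver. The pupil-level t-test also gives an interval that is too narrow, because pupils in the same school are treated as independent.

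**Working it through.** **Inputs from the article.** 43 per group before attrition; 50 per group enrolled; 2 schools per arm; 25 pupils per school; 12 stage 2 schools (6 per sex).

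**Assumptions.** Two-sided alpha 0.05; power 80% or 90%; ICC 0.02 to 0.05. The article gives none of these.

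**1. What 43 implies.** Delta/S = √2 × (1.96 + Z₁₋β)/√43.
- 80% power: √2 × 2.80/6.56 = 0.604.
- 90% power: √2 × 3.24/6.56 = 0.699.

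A round 0.70 at 90% power gives exactly 43. A round 0.60 at 80% gives 44. The article does not say which was used.

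**2. Attrition.** 43 × 1.15 = 49.45, rounded up to 50. If 43 per arm complete, each school contributes 43/2 = 21.5 completers, and this figure is used below.

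**3. Between-school df.**
- Stage 3: 4 schools − 2 arms = 2, or 1 with sex as an additive term. Within arm-by-sex cells it is 0.
- Stage 2: (6 − 1) + (6 − 1) = 10 within sex. Adjusting for school sector leaves 9, and other school-level covariates leave fewer.

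**4. Standard error of the arm contrast, in SD units.** SE = √(2/2 × [ICC + (1 − ICC)/21.5]).
- No school variance (the planned t-test): √(1/21.5) = 0.216
- ICC 0.02: √(0.02 + 0.98/21.5) = 0.256
- ICC 0.05: √(0.05 + 0.95/21.5) = 0.307

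**5. 95% half-widths.**

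| Analysis | t | ICC 0.02 | ICC 0.05 |
|---|---|---|---|
| Planned pupil-level t-test (84 df) | 1.99 | 0.43 (school variance ignored) | 0.43 (school variance ignored) |
| Stage 2 school variance, 10 df | 2.23 | 0.57 | 0.68 |
| Stage 2 school variance, 9 df | 2.26 | 0.58 | 0.69 |
| Stage 3 alone, 2 df | 4.30 | 1.10 | 1.32 |
| Stage 3 alone, 1 df | 12.71 | 3.25 | 3.90 |

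Putting the whole SE on 9 or 10 df is an approximation.

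**6. Detectable difference with a 10 df variance.** (t₀.₉₇₅ + t₁₋β) × SE.
- 80% power: (2.228 + 0.879) × 0.256 = 0.80 SD; × 0.307 = 0.95 SD. On 9 df these are 0.81 and 0.97 SD. Compare 0.60 SD from step 1.
- 90% power: (2.228 + 1.372) × 0.256 = 0.92 SD; × 0.307 = 1.11 SD. Compare 0.70 SD.

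**7. Error rate of the planned test.** The design effect is 1 + 20.5 × ICC, which is 1.41 at ICC 0.02 and 2.03 at 0.05. A nominal 5% test then rejects with probability 2[1 − Φ(1.96/√1.41)] = 9.9%, or 16.8% at ICC 0.05.

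**8. How well stage 2 fixes the ICC.** With an assumed 300 pupils (30 items × 10) and an observed ICC of 0.05, the 95% interval is about 0.004 to 0.20. From stage 3 on 2 df it is about 0 to 0.78.

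**9. Only if 43 rested on a borrowed S.** If the true S were 25% larger, the 0.604 becomes 0.604/1.25 = 0.483, and pupil-level power falls from 80% to Φ(0.483/0.216 − 1.96), about 61%. Starting from 0.70 at 90%, it falls to about 74%.

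**The case against.** **The formula needs only a ratio.** Delta/S can be set directly as a standardized effect, and 0.70 at 90% power gives exactly 43. A reader might infer that 43 rests on a wrong S. The article does not show that, so step 9 is conditional. Under this reading two things remain unknown: the score difference that the ratio represents, and the between-school variance.

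**The article is condensed.** The source of Delta/S and further uses of the stage 2 data may be in a fuller protocol. It cannot be said that those data will go unused, only that the article names no such use. The printed formula, the four-school allocation and the planned t-tests are stated, and the point rests on these. Verb tenses are mixed and recruitment began before the protocol version date, so the order of events is not fully clear either.

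**Stage 3 has some information of its own.** A reader might say that it cannot estimate school variance at all. That is exact only within arm-by-sex cells. Otherwise there are 1 or 2 df, too few to be useful but not none.

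**Stage 2 variance is a different quantity.** It comes from one cross-sectional measurement of whole classes, and schools of different age levels will inflate it. Stage 3 compares post-test or baseline-adjusted scores. This stands. It is a reason to show a range and not to let the external variance be the only basis for inference.

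**The remedy does not rescue the trial.** A reader might hope that borrowing the variance makes the interval workable. A half-width of 0.57 to 0.68 SD is about as wide as the effect implied by 43. This also stands.

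**Conclusion.** The point holds in a limited form. The stated size omits a variance that the design makes essential. Stage 2 could estimate it far better than stage 3 can, and the article gives stage 2 no such task. Under two-sided 5%, 21.5 completers per school and ICCs of 0.02 to 0.05, the detectable difference at 80% power is about 0.8 to 1.0 SD, not 0.60 SD. The planned t-test reports a half-width of 0.43 SD where 0.57 to 0.68 SD would be more honest. The ICCs, alpha and power are assumptions; the number of schools, the pupil-level formula and the t-tests are the article's own. It is not established that 43 is arithmetically wrong, that its S is wrong, or that stage 2 data would make a four-school comparison precise.

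**What to change.** Before the stage 3 comparison:

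1. From the 12 stage 2 schools, fit a mixed model to the questionnaire score with sex and age, and with school sector if the df allow. Report the SD and the within-sex between-school variance with its confidence interval.
2. State whether 43 came from a standardized effect or from a Delta and an S, and give the score difference it corresponds to.
3. Restate the difference that 100 pupils in four schools can detect, using about 21.5 completers per school and the interval from item 1.
4. Replace the pupil-level t-test standard error with one that includes the stage 2 between-school variance, shown over its plausible range. Report the 1 to 2 df school-level analysis beside it.

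The cost is one model run on data already planned and a paragraph of text, with no extra pupils or schools. The downsides should be stated. The stage 2 variance is cross-sectional and may not carry over to post-test or baseline-adjusted scores, the interval stays wide, and the stated detectable difference becomes less favourable.
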